## Abstract

**Background:**

Cataract remains the leading cause of reversible blindness worldwide, particularly in older adults, in whom capsular weakness during phacoemulsification may preclude posterior chamber intraocular lens (IOL) implantation. In such scenarios, alternative fixation methods such as scleral-sutured and iris-claw lenses are preferred. However, direct comparative evidence regarding their safety, stability, and postoperative visual outcomes during primary cataract surgery is limited.

**Objective:**

This study aims to compare the surgical and visual outcomes between retropupillary iris-claw IOL implantation and scleral-sutured fixation of single-piece foldable IOLs performed during primary cataract surgery by phacoemulsification in patients with inadequate capsular support.

**Methods:**

This is a prospective, 2-arm, open-label randomized controlled trial being conducted at the Department of Ophthalmology, Acharya Vinoba Bhave Rural Hospital, Sawangi, India. A total of 92 patients aged 35 to 75 years with intraoperative posterior capsular compromise will be randomized (block randomization, sealed opaque envelopes) into 2 groups: group A (retropupillary iris-claw IOL) and group B (scleral-sutured IOL). Preoperative, intraoperative, and postoperative data will be collected at day 1, day 15, day 30, and day 90. The primary outcomes are best-corrected visual acuity and lens-induced astigmatism at 3 months. Secondary outcomes include IOL centration or tilt, intraoperative and postoperative complications, and patient satisfaction (assessed using the National Eye Institute Visual Function Questionnaire-25). Data will be analyzed using ANOVA and mixed-effects models.

**Results:**

Recruitment commenced in March 2025 and is expected to conclude by September 2025, with interim data analysis scheduled for November 2025. As of the current submission, patient enrollment is ongoing, and no interim results have been analyzed.

**Conclusions:**

This randomized protocol is designed to generate comparative clinical evidence on the efficacy, safety, and visual stability of iris-claw and scleral-sutured IOL fixation in primary cataract surgery. The findings will contribute to optimizing surgical decision-making in cases with deficient posterior capsular support.

## Introduction

### Overview

Cataract remains the leading cause of reversible blindness worldwide and continues to impose a major public health burden, particularly among older adults in low- and middle-income countries [1]. In 2020, an estimated 79 million individuals aged 50 years and older were affected globally, representing a 39% increase in prevalence since 1993 [2]. The only definitive treatment is surgical extraction of the opacified lens followed by intraocular lens (IOL) implantation [3]. Phacoemulsification with posterior chamber IOL placement is the preferred modern technique due to its faster recovery, smaller incision size, and superior visual outcomes [4]. However, intraoperative or pre-existing capsular rupture can complicate surgery and preclude standard posterior chamber fixation, resulting in aphakia and unstable visual rehabilitation [3,5].

When the posterior capsule is compromised, secondary fixation techniques are required to achieve optical stability. The 2 widely practiced approaches are retropupillary iris-claw IOL fixation and scleral-sutured posterior chamber IOL fixation [6]. In iris-claw implantation, the lens is enclavated onto the midperipheral iris, providing a relatively simple and reproducible procedure with shorter operative time [5]. Conversely, scleral-sutured fixation secures the IOL haptics within scleral flaps using 10‐0 polypropylene (Prolene; Ethicon) sutures, offering stable posterior chamber positioning and a reduced risk of endothelial trauma but requiring greater surgical expertise [7]. Both techniques have evolved substantially, yet each carries distinct risks, such as iris chafing, pupil distortion, or suture degradation [8,9].

Comparative evidence between these 2 fixation methods primarily originates from retrospective or heterogeneous secondary IOL implantation studies [7,8]. A limited number of prospective randomized studies have evaluated their performance in primary cataract surgeries where capsular support is inadequate at the index operation. Existing studies report conflicting outcomes: some suggest lower intraoperative complications with iris-claw IOLs [7], while others demonstrate superior centration and long-term stability with scleral fixation [8,9]. Moreover, data on lens-induced astigmatism, patient-reported visual satisfaction, and postoperative quality of life remain scarce. The choice between scleral-sutured and retropupillary iris-claw fixation in primary cataract surgery requires solid evidence on their safety, effectiveness, and patient experience. This randomized trial addresses that gap by directly comparing both techniques under standardized surgical conditions. It will assess visual outcomes, complications, and patient-reported satisfaction to help guide reliable IOL selection when posterior capsular support is inadequate.

### Research Question

Among adult patients undergoing primary cataract surgery by phacoemulsification with inadequate posterior capsular support, does retropupillary iris-claw IOL implantation provide comparable or superior visual and surgical outcomes compared with scleral-sutured fixation of single-piece foldable IOLs?

### Hypothesis

This randomized controlled trial hypothesizes that retropupillary iris-claw IOL implantation will achieve visual outcomes (measured by best-corrected visual acuity [BCVA] and lens-induced astigmatism at 3 months) that are noninferior or superior to those obtained with scleral-sutured fixation. It is further hypothesized that the iris-claw technique will demonstrate shorter operative time and fewer intraoperative and postoperative complications, while maintaining comparable centration and patient-reported satisfaction scores.

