### Data Management and Statistical Analysis

Statistical methods used for data management and analysis are summarized in this section. Continuous variables (eg, BCVA, astigmatism, and intraocular pressure) will be summarized as mean (SD) and analyzed using the independent *t* test for between-group comparisons and repeated-measures ANOVA for longitudinal analysis. Categorical variables (eg, complications and sex) will be compared using the chi-square test or the Fisher exact test. Multivariate analysis will be performed using mixed-effects linear regression to adjust for baseline covariates (age and preoperative vision). Missing data will be handled using multiple imputation under a missing-at-random assumption. Interim analysis will be conducted after 50% enrollment to evaluate safety and adherence; no stopping rules for efficacy are planned. Statistical analyses will be performed using SPSS software (version 27.0; IBM Corp). A *P* value <.05 will be considered statistically significant.

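### The hypothesis allows a noninferior or comparable conclusion, but the stated decision rule (difference tests at P<.05, with no margin or confidence-interval rule in the text shown) cannot establish one

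*Protocol article*

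**What the plan says.** The Research Question section of the protocol article asks whether iris-claw implantation will "provide comparable or superior visual and surgical outcomes compared with scleral-sutured fixation". The Hypothesis section names BCVA and lens-induced astigmatism at 3 months, the two primary outcomes, and expects iris-claw results "that are noninferior or superior to those obtained with scleral-sutured fixation". It adds that the technique should have fewer complications "while maintaining comparable centration and patient-reported satisfaction scores".

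The Data Management and Statistical Analysis section assigns continuous outcomes to an independent t test "for between-group comparisons and repeated-measures ANOVA for longitudinal analysis", and adds a mixed-effects linear regression adjusted for age and preoperative vision. The only criterion for a conclusion is that a P "value <.05 will be considered statistically significant". The section gives no margin in logMAR or dioptres, no confidence-interval criterion and no sequence from noninferiority to superiority.

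The Abstract gives the size: "A total of 92 patients aged 35 to 75 years with intraoperative posterior capsular compromise will be randomized". Allocation is 1:1 (Randomization, Allocation Concealment, and Blinding). The Eligibility Criteria section refers the sample size calculation to Multimedia Appendix 1, which is not shown.

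**The concern.** A claim of noninferiority says that the new technique is not worse by more than a stated amount. It needs that amount, and a rule that uses the confidence interval or an equivalent one-sided test against the margin. The t test, the repeated-measures ANOVA and the mixed model, as described, each test a null hypothesis of no difference. P<.05 can show that the arms differ. P≥.05 shows only that a difference was not demonstrated, and it becomes more likely as the data become less precise.

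The stated rule can therefore settle the superior half of the hypothesis but not the noninferior half, nor the comparable half of the research question. The trial is meant to guide the choice of lens when capsular support is inadequate. A non-significant result is quite possible, and the text as it stands fixes no valid way to say what that result means.

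**Working it through.** **1. Hypothesis against rule.**

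| Claim in the article | What would establish it | What the analysis section provides |
|---|---|---|
| Superior on BCVA and astigmatism | Test of no difference, P<.05 in the favourable direction | Yes |
| Noninferior on BCVA and astigmatism | Confidence limit compared with a prespecified margin | No margin, no interval rule |
| Comparable visual and surgical outcomes | As for noninferiority, or two-sided equivalence limits | No margin, no limits |

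The mismatch follows from the text alone. The arithmetic below only shows its size for BCVA.

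**2. Inputs.** From the documents: 92 patients at 1:1, so 46 per arm; t test; .05 level. Assumed, because the text shown does not give them: two-sided testing; logMAR SD of 0.15, 0.20, 0.25 or 0.30; a deficit of 0.10 logMAR (one line) as the illustration; no dropout; no covariate adjustment. The planned 92 cannot be reproduced, because the effect size, SD, power and dropout behind it are not in the text shown.

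**3. Precision.** Standard error of the difference = SD × √(2/46) = SD × 0.2085. The 95% half-width = t(0.975; 90 df) × SE = 1.987 × SE. For SD 0.20: SE = 0.0417, half-width = 0.083 logMAR.

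**4. Chance of missing a true deficit of 0.10 logMAR.** The noncentrality is 0.10/SE. The probability of P≥.05 comes from the noncentral t distribution with 90 degrees of freedom. For SD 0.20: 0.10/0.0417 = 2.40, giving 34%. A normal approximation agrees to about one percentage point (33%).

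**5. Margin that 46 per arm could test.** At one-sided 2.5%, 80% power and a true difference of 0: margin = (1.96 + 0.84) × SE. For SD 0.20: 2.80 × 0.0417 = 0.117 logMAR.

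**6. Power and size for an illustrative margin of 0.10 logMAR.** Power with 92 patients = Φ(0.10/SE − 1.96). Total N for 80% power = 2 × 2 × (2.80 × SD/0.10)², with each arm rounded up.

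| Assumed SD | 95% half-width | P(non-significant), true 0.10 deficit | Margin at 80% power | Power at N = 92, margin 0.10 | Total N for 80% power, margin 0.10 |
|---|---|---|---|---|---|
| 0.15 | 0.062 | 11% | 0.088 | 89% | 72 |
| 0.20 | 0.083 | 34% | 0.117 | 67% | 126 |
| 0.25 | 0.104 | 52% | 0.146 | 48% | 198 |
| 0.30 | 0.124 | 65% | 0.175 | 36% | 284 |

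The 0.10 margin is for illustration only and is not proposed for the trial. No equivalent table is given for astigmatism, because the text shown offers neither an SD nor a reference difference in dioptres.

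**The case against.** Several points on the other side are fair.

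*A margin may exist elsewhere.* A sample size based on noninferiority needs one, and Multimedia Appendix 1 or an analysis plan may hold it. A reader might infer that the trial has no margin at all. The documents do not support that: it can be said only that none appears in the text shown. The mismatch remains, because the article does not leave the decision rule to another document. It states one, and that rule tests for a difference. If a margin exists, the analysis section has to be reconciled with it.

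*This may be a difference trial with a loosely worded hypothesis.* The Objective and Study Design sections say only that the techniques will be compared, and the Hypothesis section does not rank noninferior above superior. So the documents do not establish that noninferiority is the main claim. This stands, and it is why changing the wording is a full remedy and not a fallback.

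*Nobody says that P≥.05 will be called noninferior.* This is correct. A reader might infer that the investigators plan to do so, but no section says it. The point is that the rule cannot deliver that conclusion.

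*The analyses themselves are usable.* The t test and the mixed model both yield an estimated difference and its interval. What is lacking is a margin and a rule for reading the interval, not a different model. Adjustment for preoperative vision could also reduce the residual SD and improve on the unadjusted figures.

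A reader might also infer that a significant but trivially small deficit would count as failure. That does not fit this sample size. An observed difference must exceed the half-width to be significant, so at an SD of 0.20 or more no BCVA difference below about 0.08 logMAR could reach P<.05.

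**Conclusion.** The concern holds as a conflict between the stated hypothesis and the stated decision rule. In the text shown, the rule can establish a difference but not noninferiority or comparability. That conclusion rests on no assumed figure.

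The size does rest on assumptions. With 46 per arm, two-sided .05 testing, no dropout and logMAR SDs of 0.15 to 0.30, a true deficit of 0.10 logMAR would be non-significant with probability of about 11% to 65%, and the 95% half-width is about 0.06 to 0.12 logMAR. At an SD of 0.25 or more the half-width exceeds 0.10 logMAR, so even an estimate of no difference would leave a deficit of that size inside the interval. Dropout would worsen these figures, and covariate adjustment could improve them. The label of superiority test and its two-sidedness are inferences from a t test at P<.05; the article states neither.

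**What to change.** Before any outcome data are compared by arm, take one of two courses.

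**(a) Keep the noninferiority claim.** State a clinically justified margin for Day 90 BCVA in logMAR and one for lens-induced astigmatism in dioptres, and say whether both must be met. Larger values are worse on both scales. So declare noninferiority if the upper limit of the two-sided 95% confidence interval for iris-claw minus scleral-sutured lies below the margin, and superiority if it also lies below 0. State the power that 92 patients give for those margins and accept that it may be low; the margin must not be chosen to suit the sample size. If Multimedia Appendix 1 already contains a margin, carry it into the analysis section.

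**(b) Drop the claim.** Remove the noninferior and comparable wording from the Research Question and Hypothesis sections, and state that P≥.05 will be reported as inconclusive, with its confidence interval.

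Either course is an amendment of a few sentences, with the prior ethics approval and registry update that the article already requires for amendments. Course (b) needs no further patients or visits. Course (a) needs none if the power at 92 is accepted. If it is not, recruitment would have to grow: the illustrative 0.10 logMAR margin needs a total of 126, 198 or 284 for SDs of 0.20, 0.25 or 0.30. The Results section says that no interim data have been analyzed, so on the article's own account a margin can still be set credibly. One chosen after the arms have been compared could not be.

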## Methods

### Study Design

This will be a prospective, hospital-based, 2-arm, open-label randomized controlled trial designed to compare the surgical and visual outcomes between retropupillary iris-claw IOL implantation and scleral-sutured fixation of single-piece foldable IOLs in patients undergoing primary cataract surgery by phacoemulsification. The trial will be conducted at the Department of Ophthalmology, Acharya Vinoba Bhave Rural Hospital (AVBRH), Sawangi, Wardha, India.

### Study Setting

All surgical and postoperative procedures will be performed in the dedicated ophthalmic operation theaters of AVBRH under standardized aseptic conditions by trained consultant ophthalmic surgeons. Each participating surgeon will have independently performed at least 30 cases of both iris-claw and scleral-sutured IOL fixation techniques to ensure procedural consistency.

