### Randomization, Allocation Concealment, and Blinding

Eligible patients will be randomly allocated in a 1:1 ratio into 2 groups: group A (retropupillary iris-claw IOL) and group B (scleral-sutured fixation). A computer-generated block randomization sequence (block size of 4) will be prepared by an independent statistician. The group assignment will be concealed in sequentially numbered, opaque, sealed envelopes opened only after capsular deficiency confirmation during surgery.

Due to the nature of the interventions, blinding of surgeons and patients will not be feasible. However, postoperative outcome assessors and data analysts will remain blinded to the intervention group to minimize observer bias. Postoperative assessors will follow standardized grading protocols and will remain masked to group assignment to reduce detection bias.

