## Discussion

Management of aphakia during cataract surgery remains a critical surgical challenge, particularly when posterior capsular rupture or zonular instability precludes in-the-bag IOL implantation [11,12]. Although several fixation techniques have been developed, the comparative efficacy and safety of scleral-sutured and retropupillary iris-claw fixation during primary cataract surgery remain insufficiently explored [13]. This protocol aims to prospectively evaluate these two commonly used methods under standardized conditions. The rationale for comparing scleral-sutured and iris-claw fixation stems from their distinct anatomical and procedural advantages. Retropupillary iris-claw lenses offer a posterior chamber position similar to that of an in-the-bag IOL while avoiding contact with the corneal endothelium and anterior chamber angle [2,3]. They are relatively simple to implant, require shorter surgical time, and provide satisfactory centration with minimal postoperative astigmatism [5,7]. Conversely, scleral-sutured fixation restores a near-physiological IOL position behind the iris plane and has been associated with excellent visual outcomes and long-term stability [8]. However, it demands greater surgical skill and carries the potential of suture-related complications, including knot erosion and late dislocation [14,15].

Several retrospective and comparative studies have examined the outcomes of these techniques, but most involve heterogeneous populations or secondary IOL implantations. Madhivanan et al [5] demonstrated that both retropupillary iris-claw and scleral-fixated IOLs achieve significant improvement in BCVA, although scleral fixation required longer surgical duration. Similarly, Durmus et al [7] reported comparable visual outcomes but found that endothelial cell loss was lower with iris-claw lenses than with sutureless scleral fixation. Shahid et al [8] emphasized that scleral fixation provides superior long-term centration yet remains technically demanding and time-intensive. These findings justify the need for a prospective, randomized evaluation focusing specifically on primary cataract cases rather than secondary or complicated aphakia.

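### Operating surgeon is absent from both the stated randomization and the stated covariates, at a modest cost in precision

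*Protocol article*

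**What the plan says.** Under Study Setting, the protocol article has operations done "under standardized aseptic conditions by trained consultant ophthalmic surgeons". It sets one experience criterion for them: "Each participating surgeon will have independently performed at least 30 cases of both iris-claw and scleral-sutured IOL fixation techniques to ensure procedural consistency".

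The article does not treat the techniques as equally hard. The Introduction (Overview) describes scleral suturing as offering a "reduced risk of endothelial trauma but requiring greater surgical expertise", and the Discussion says of it that "it demands greater surgical skill and carries the potential of suture-related complications". The Discussion also presents iris-claw lenses as comparatively simple and quicker to implant.

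Under Randomization, Allocation Concealment, and Blinding, "Eligible patients will be randomly allocated in a 1:1 ratio into 2 groups", and "A computer-generated block randomization sequence (block size of 4) will be prepared by an independent statistician". No stratification factor is named.

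Under Data Management and Statistical Analysis, the between-group comparison of continuous outcomes is an independent t test. The adjusted analysis is "mixed-effects linear regression to adjust for baseline covariates (age and preoperative vision"). Surgeon is not on that list, and the random effects of the model are not named.

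Intervention Procedures adds uniform protocols and periodic video review by the data monitoring committee, aimed at standardizing technique between surgeons.

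**The concern.** The article recognizes differences between surgeons as something to control, and controls them before and during surgery. It does not carry them into the comparison. A floor of 30 cases says nothing about experience above 30. If one technique is harder, the same floor can leave surgeons further apart on that technique than on the other.

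Surgical duration, complications, centration and astigmatism are all outcomes that the operator plausibly affects. When surgeon is in neither the allocation scheme nor the model, two things follow:

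- differences between surgeons stay in the residual variance of the arm comparison;
- by chance, a surgeon with better or worse results may contribute more cases to one arm.

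With 46 patients per arm, precision is worth recovering if it costs little.

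**Working it through.** **Inputs from the protocol article.** Total 92 (Abstract, Methods), 1:1, so 92/2 = 46 per arm; blocks of 4; significance at .05, taken as two-sided. The effect size, SD and power behind 92 are in an appendix that is not shown, so 92 cannot be rebuilt. The point does not depend on it.

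**Assumptions.** The article gives neither the number of surgeons nor the share *r* of outcome variance that lies between surgeons. I use *r* = 5% to 15% and 2 to 6 surgeons.

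**Step 1. Baseline precision, in outcome SD units.** The standard error of the arm difference is √(2/46) = 0.209. The difference detectable with 80% power is (1.960 + 0.842) × 0.209 = 0.58 SD.

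**Step 2. Gain from adjusting for surgeon.** Adjustment removes the between-surgeon share, so SE = √(2(1 − r)/46). Power is Φ(0.584/SE − 1.960), and the number of patients giving the unadjusted precision is 92(1 − r).

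| r | SE | Power | Patients needed to match unadjusted 92 |
|---|---|---|---|
| 0 | 0.209 | 80% | 92 |
| 5% | 0.203 | 82% | 88 |
| 10% | 0.198 | 84% | 83 |
| 15% | 0.192 | 86% | 79 |

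These ignore lost degrees of freedom. As a fixed effect, *k* surgeons use *k* − 1, so six surgeons use 5.

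**Step 3. Size of the chance imbalance.** I simulated 92 patients in unstratified blocks of 4, spread at random over equally busy surgeons, with *r* = 10% and 4,000 runs per setting. The shift in the arm difference caused by surgeon imbalance has an SD of 0.047, 0.053, 0.057 and 0.063 outcome SDs for 2, 3, 4 and 6 surgeons. With blocks stratified by surgeon it would be 0.006 to 0.014. Against the standard error of 0.209, the unstratified shift contributes (0.047/0.209)² = 5% to (0.063/0.209)² = 9% of the variance. Steps 2 and 3 are two views of the same cost and should not be added.

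**Step 4. Validity of the unadjusted test.** In a simulation with 3, 4 or 6 surgeons and *r* of 5%, 10% or 15%, the type I error of the t test stayed between 4.8% and 5.7%, which is nominal within simulation error.

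**The case against.** The strongest reply is that this is silence rather than error. The article condenses a fuller protocol, and the analysis plan is not shown. The parenthesis lists baseline covariates, whereas surgeon is a clustering factor that might sit among the unnamed random effects. The article also does not say in so many words that one unstratified sequence serves all surgeons. This stands in part: if the full plan includes surgeon, one sentence settles the matter. But the article does state an adjustment set, and surgeon is not in it.

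It is also fair that the experience floor is not the only safeguard. A standardized phacoemulsification technique, uniform perioperative protocols, a common definition of inadequate support and video review may all narrow differences between surgeons. They argue for the lower end of the assumed range. They do not put surgeon into the comparison.

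Three stronger readings are tempting, and the documents do not support them:

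- **Bias.** A reader might infer that the comparison is systematically distorted. Allocation is randomized and concealed until capsular deficiency is confirmed during surgery, and each surgeon has experience of both techniques. The t test's standard error already contains the surgeon variance.
- **Lopsided caseloads.** A reader might count how often at least one surgeon's cases split 65:35 or worse. That figure depends on the number of surgeons and on the cut-off. With equal caseloads it is under 1% for 2 surgeons, about 8% for 3, 42% for 4 and about 75% for 6. With 4 surgeons and 23 cases each, 15:8 is 65.2%, so moving the cut to 66:34 lowers 42% to about 18%. It does not measure the effect on the arm difference; step 3 does.
- **Technique versus proficiency.** A reader might expect the adjusted model to separate an effect of the technique from an effect of surgeons' skill in it. That is a surgeon-by-technique interaction, which a surgeon main effect does not remove. The article also treats greater technical demand as a feature of scleral fixation, so results among qualified consultants arguably belong to the question asked.

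**Conclusion.** The point holds as one of efficiency and transparency, not of validity. The stated randomization and the stated covariates both omit surgeon, although several surgeons operate and the article itself calls the techniques unequal in difficulty. The loss is modest: about 2 to 6 points of power from a nominal 80%, and, at a 10% surgeon share, a chance shift with an SD of about 0.05 to 0.06 outcome SDs against a standard error of 0.21. Both figures rest on an assumed surgeon share and number of surgeons, so even this gain is not established. It is worth making because it costs so little. Whether an arm difference reflects technique or proficiency can be examined only in a descriptive table by surgeon, which cannot settle it with 92 patients.

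**What to change.** Before any data are seen by arm:

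- Prespecify operating surgeon in the mixed-effects model already planned, alongside age and preoperative vision, for BCVA, astigmatism and surgical duration. Use a fixed effect if there are few surgeons and a random intercept if there are many.
- State a rule for pooling surgeons with very few cases.
- Tabulate allocation and outcomes by surgeon and arm, as description only.

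If the full analysis plan already includes surgeon, say so in the article.

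Recruitment began in March 2025, so the remedy is placed in the analysis; the envelopes need not change. The cost is a few lines of analysis text, one table and a few degrees of freedom out of 92 patients. The sample size and surgical procedures are untouched.
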